### Analysis:

The confirmatory, primary analysis will be performed following the intention-to-treat (ITT) principle. The efficacy of the intervention will be quantified using two-level linear regression stratified by type of medical treatment (insulin vs. non-insulin therapy). The effect of the intervention on the primary outcome will be adjusted for baseline values in SDSCA-G. Secondary analyses (related to the secondary objectives) will be performed according to ITT principle as well, followed by a complete case analysis as sensitivity analysis to assess the robustness of effect estimates. To relate cost differential to outcome differential between intervention and control group the incremental cost effectiveness ratio will be calculated. We will apply bootstrap methods to model uncertainties in costs. Maximum willingness to pay thresholds and cost-acceptability curves will be determined. Sensitivity analyses will provide information on robustness of assumptions.

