## 7. Randomization

Patients will be randomly allocated to case management (PTC) or usual care (TAU) at individual-level in the ratio of 1:1 stratified by

- (i) type of medical treatment (insulin vs. oral medication/no medication) of their index disease (type 2 diabetes) and
- (ii) study center (PCP).

Type of medical treatment has been identified as the strongest predictor of diabetes self-care in the preceding (unpublished) scoping review, and is thus captured by a physician reported questionnaire to serve as validated stratification criteria. We will hence perform stratified block randomization with variable block lengths to ensure study groups of approximately equal size. The block sizes will not be disclosed, to ensure concealment. Instead, this specific information will be provided in a separate document with restricted access only to the randomization authority. The randomization procedure is closely linked to the data collection procedure (see Chapter 10) in so far as that it is performed centrally using the ICW Care Manager as platform.

All eligible patients participating in the study will be registered in the software during a three-month wash-in phase, along with the physician-reported information about eligibility criteria (see Chapters 5 & 6) and type of medical therapy. The ICW Care Manager contains virtual folders for the two groups (PTC vs. TAU) within participating primary care practices.

The randomization authority (a designated person not involved in care of the trial patients and analysis of data) will access the database of registered patients in a weekly interval to monitor the recruitment process. Recruited and registered patients who fulfill the inclusion criteria will be centrally randomized (stratified by type of medical therapy and PCP) to PTC vs. TAU using a computerized random number generator to create randomization lists for each stratum. The allocation will be documented separately in an Excel file with restricted access except for the randomization authority.

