### 11.2 Statistical hypotheses, methods and analyses

The primary objective of this study is to determine the effectiveness of a complex intervention compared to usual care. The primary efficacy endpoint is the change in SDSCA-G score from baseline (To) to 9 months after baseline (T1), i.e. the difference SDSCA-G T1–To. The study objective will be statistically formulated as a test of the null hypothesis  $H_0: \mu_1 = \mu_2$  (the mean difference SDSCA-G T1–To is equal in the two groups) against the alternative hypothesis  $H_1: \mu_1 \neq \mu_2$  (the mean differences SDSCA-G T1–To are different in the two groups). The null hypothesis will be tested at the two-sided significance level of  $\alpha=0.05$ .

The primary efficacy analysis will use a multilevel regression approach with patients at level one and NCMs at level two. The primary model will include treatment group as fixed factor, NCMs as random factor with the baseline value of SDSCA-G and type of medical treatment as covariates. The results will be presented as the mean between-group difference in SDSCA-G T1–To with the corresponding 95% confidence interval. The associated Cohen's effect size  $d$  will be calculated. To support the primary analysis, all potentially relevant baseline characteristics will be added as covariates to the model in sensitivity analyses. A further sensitivity analysis of the primary endpoint will include an unadjusted two-sample t-test on change in SDSCA-G from baseline to 9 months after baseline. Results from these sensitivity analyses will serve to explain and interpret the results of the primary analysis.

The primary analysis will be performed adhering to the intention-to-treat principle. An additional sensitivity analysis will be conducted on a per-protocol analysis set.

The statistical analyses of the secondary endpoints numbered 1-6 (see pages 4-5) will use the same multilevel approach as the primary analysis. According to the scaling of the considered endpoint, a linear or logistic two-level regression model will be fitted. The results will be presented in an analogous manner to the primary analysis. All statistical tests will be two-sided at the significance level of  $\alpha=0.05$ .

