## **11.4 Sample size calculation**

Sample size was calculated based on the expected difference between the two treatment groups in mean change in the SDSCA-G score from baseline (T0) compared to 9 months after baseline (T1). Based on data from published studies, which used the revised SDSCA as outcome measure (53-55) we estimated a mean change of 0.5 days (standard deviation 2.0) in the overall SDSCA-G “score” (calculated as the sum of days of items 1 - 10 divided by 10) per patient in 9 months as minimal clinically relevant change.

Based on these estimates, a total of 506 patients (253 per arm) would be required to detect an effect size (Cohen’s d) of 0.25 between-groups (PTC vs. TAU) (50% relative increase in self-care) with a power of 80 % applying a two-sided t-test for two independent samples at a significance level of 5%.

Assuming a drop-out rate of 15% over the period of 9 months, the overall required sample size amounts to a total of 582 participants (291 per arm).

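### Randomization is stratified by practice (PCP), but the primary model has no PCP term and NCM replaces it only in part, so the test is mildly conservative

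*Protocol*

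**What the plan says.** Protocol section 7 (Randomization) names two stratification factors, type of medical treatment and study center. Patients "will be centrally randomized (stratified by type of medical therapy and PCP) to PTC vs. TAU", by block randomization with variable block lengths.

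Protocol section 11.2 writes out the confirmatory model. Patients are level one and NCMs level two, treatment group is a fixed factor, and the other terms are "NCMs as random factor with the baseline value of SDSCA-G and type of medical treatment as covariates". PCP does not appear. The sensitivity analyses in that section (further baseline characteristics, an unadjusted t-test, the per-protocol set) do not name it either. The models for secondary endpoints 1-6 use the same approach.

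The Summary (Analysis) describes a "two-level linear regression stratified by type of medical treatment (insulin vs. non-insulin therapy") and does not mention PCP.

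On NCMs, section 8 gives 11 NCMs for 30 PCPs, each caring for about 26 patients from about 3 PCPs. One Turkish-speaking NCM is assigned by language or cultural preference. Sections 8 and 15 restrict NCM access to intervention-arm patients.

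**The concern.** Blocking within practice balances the arms within each PCP and so removes between-practice variance from the treatment contrast. A model that ignores practice still counts that variance in its residual. The estimated standard error then exceeds the true one, coverage is above 95%, and some power is lost. Of the two factors used to stratify, the model keeps one and drops the other without giving a reason.

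NCM does not repair this. Several practices share one NCM, so most practice variance can remain within the NCM level. NCMs also have no TAU patients: 11 x 26 = 286, about one arm of 291. A control patient therefore has an NCM value only by convention, and the protocol states none.

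**Working it through.** **Inputs from the protocol.** Section 11.2: two-sided alpha of 0.05. Section 11.4: "we estimated a mean change of 0.5 days (standard deviation 2.0"), so d = 0.5/2.0 = 0.25. The evaluable number is given as "a total of 506 patients (253 per arm) would be required to detect an effect size". It rests on a two-sided two-sample t-test with 80% power. An allowance of 15% for losses by month 9 brings the total to 582. Section 7: 1:1 allocation. Sections 8 and 9.1: 30 PCPs, 11 NCMs.

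**Assumption.** The protocol gives no between-PCP ICC (rho) for the change score. The range 0.01 to 0.10 is shown.

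**Step 1: the plan's own figure.** The two-sample t-test (noncentral t) gives 253 per arm with power 80.1%, so 506 is reproduced. The normal approximation gives 252 per arm, and its power at N = 506 is 80.3%.

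**Step 2: true variance of the treatment difference.** With balance within PCP and total SD 2.0:

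Var(true) = 4 x 2.0² x (1 - rho) / N = 16(1 - rho)/506.

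**Step 3: variance the planned model estimates.** Suppose every TAU patient is coded to the NCM of the practice. With about 3 PCPs per NCM and independent practice effects, the NCM factor takes up about 1/3 of the PCP variance and 2/3 stays in the residual:

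Var(planned) = 16(1 - rho + (2/3)rho)/506.

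**Step 4: consequences.** r = sqrt(Var(planned)/Var(true)); type I error = 2(1 - Phi(1.96 r)); power = Phi(0.5/SE(true) - 1.96 r).

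Example, rho = 0.05: SE(true) = sqrt(16 x 0.95/506) = 0.1733; r = sqrt(0.9833/0.95) = 1.0174. Type I error = 2(1 - Phi(1.994)) = 0.0461. Power = Phi(2.885 - 1.994) = 81.35% as planned, against Phi(2.885 - 1.960) = 82.25% with PCP in the model.

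| Assumed ICC | SE overstated | Type I error, planned | Power, planned | Power, PCP in model | Loss (points) |
|---|---|---|---|---|---|
| 0.01 | 0.3% | 4.9% | 80.5% | 80.7% | 0.2 |
| 0.05 | 1.7% | 4.6% | 81.3% | 82.2% | 0.9 |
| 0.10 | 3.6% | 4.2% | 82.4% | 84.2% | 1.8 |

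**Step 5: outer bound.** If NCM absorbed no practice variance, the factor 2/3 becomes 1. The SE would be overstated by 0.5% / 2.6% / 5.4%, type I error would be 4.9% / 4.4% / 3.9%, and the loss 0.3 / 1.4 / 2.7 points.

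**Step 6: simulation check.** REML random-intercept fits (30 PCPs of 17 patients, 11 NCMs, blocks within PCP and therapy type, 3,000 runs per ICC) agree in direction and size. Power with PCP against NCM only is 82.3% against 81.4% at ICC 0.05, and 83.5% against 81.5% at ICC 0.10; at 0.10 the mean interval width is 0.659 against 0.682. If half of the practice variance is shared among practices of the same NCM (ICC 0.05), the gap shrinks to 82.3% against 81.7%.

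**Step 7: dependence on the TAU coding.** Simulating other codings that the wording of section 11.2 permits (no true NCM effect, no baseline covariate, 1,500 runs per ICC) gives power at ICC 0.01 / 0.05 / 0.10 of about 77% / 74% / 69% if the NCM effect applies to PTC patients only, and about 55% / 40% / 24% if all TAU patients form one 'no NCM' level. In both, practice variance is read as NCM variance and charged to the treatment contrast. The table above holds only for coding by practice.

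**The case against.** The strongest reply is that the effect is small and errs on the safe side. The interval is too wide rather than too narrow, a positive result stays valid, and power under the planned model remains about 80%. That stands. Two further points also stand. The NCM factor takes up part of the practice variance, which the table credits. The ICC that matters is the one left after adjustment for baseline SDSCA-G and medical treatment, which may lie at the low end, where the loss is 0.2 points.

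It can also be said that section 11 defers detail to the SAP. This does not fully answer the point, because section 11.2 itself fixes both levels and every term of the confirmatory model.

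Three stronger readings are tempting and are not supported:

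- A reader might infer that the primary test is invalid or anti-conservative. With allocation balanced within practice and TAU patients coded to their practice's NCM, the error runs the other way.
- A reader might infer from Step 7 that the trial is badly underpowered. That would need a TAU coding the protocol does not state. What the document supports is that the coding is unspecified and needs fixing.
- A reader might infer from the Summary's word 'stratified' that there are two confirmatory estimates, one per treatment type. Section 11.2 states one null hypothesis, one model with medical treatment as covariate and one between-group difference, and rules out confirmatory subgroup analyses. The Summary wording is an editorial slip.

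**Conclusion.** The point holds in a limited form. The primary model omits one of the two stratification factors, and NCM is only a partial replacement. If TAU patients are coded to their practice's NCM, the standard error is too large by about 0.3% to 3.6%, and 0.2 to 1.8 points of power are given up for an assumed ICC of 0.01 to 0.10.

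This rests on 506 evaluable patients, near balance within PCP, about 3 PCPs per NCM with independent practice effects, and no allowance for the baseline covariate. The loss hardly changes if 15% of 582 drop out (582 x 0.85 = 494.7): with 494 patients the same formulas still give 0.2 / 0.9 / 1.8 points, and planned-model power at ICC 0.01 is Phi(0.5/sqrt(16 x 0.99/494) - 1.96 x 1.0034), about 79.5%.

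The change should be made because it aligns the analysis with the design at almost no cost, not because the planned result would mislead. The unstated coding of TAU patients must be settled with it, since the size of the effect depends on it.

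**What to change.** In section 11.2, add PCP as a random intercept for patients of both arms to the primary model and to the models for secondary endpoints 1-6. State in the same sentence whether the NCM factor is kept and, if so, how TAU patients enter that level.

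Do not use 30 fixed practice effects in the logistic models. With about 20 patients per PCP, and hypoglycemia analyzed only among patients at risk, practices without events could cause separation.

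In the Summary, write that the analysis is adjusted for type of medical treatment, instead of stratified by it.

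Cost: no new data or patients are needed, because the PCP number is part of each patient's pseudonym (section 15). The model becomes slightly more complex. It may be cross-classified if NCM is kept, since the Turkish-speaking NCM can cut across practices. PCP should also be carried into the multiple-imputation model. The change should be made before treatment allocation is unblinded.

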### 2.2 Secondary objectives

To assess:

1. if potential differences between both groups (PTC vs. TAU) in change of diabetes related self-care behavior compared to baseline (T0) can be sustained over an 18 months period (T2) with reduced intensity of care management and enhanced by self-monitoring of blood-glucose (whereas 'reduced intensity' refers to longer time-lags between telephone-monitoring contacts (Figure 1)).
2. if potential differences between both groups (PTC vs. TAU) in change of diabetes related self-care behavior after 9 months (T1)/18 months (T2) compared to baseline (T0) are confounded by patients' behavior at base-line and/or other important factors reported in the literature (sex, age, marital status/domestic partnerships, social status, migration status, type of comorbidity, perceived quality of health care, alcohol abuse and diabetes related emotional distress).
3. the changes for each dimension of diabetes related self-care behavior (diet, exercise, self-monitoring of blood glucose (SMBG), foot care, and smoking behavior) at T1/T2 compared to baseline (T0) between both groups (PTC vs. TAU).
4. if there are differences at T1/T2 between both groups (PTC vs. TAU) in change of glycosylated hemoglobin A1 (HbA1c %) compared to baseline (T0) among the subgroup of patients with a baseline value of HbA1c > 7.5 % (adjusted for the base-line value of HbA1c)
5. if there are differences at T1/T2 between both groups (PTC vs. TAU) in the cumulative incidence of (severe) symptomatic hypoglycemia among those patients at risk of this event during the respective observation period
6. if there are differences at T1/T2 between both groups (PTC vs. TAU) in change of health related quality of life (HRQL) and self-efficacy compared to baseline.

7. if the care management intervention is equitable in the distribution of potential health gains (self-care behavior, HbA1c% and HRQL) at T1.
8. differences between the intervention- and the control-group related to service utilization, direct and indirect costs of health care provision as well as the financial burden of informal care provided by patients' relatives at the end of observation time.

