7. The equity-efficacy ratio calculated as the ratio between the change (compared to To at T1) in SDSCA-G 'score' of items 1-10 (excluding smoking), HbA1c% and EQ-Index among the lowest vs. highest socioeconomic group (including education, occupation, income and subjective social status) in both arms of the trial (PTC vs. TAU). This includes subgroup analyses for migrant populations.
8. Further secondary outcomes will be captured by the Client Socio-demographic and Service Receipt Inventory (CSSRI) (27, 28) and the financial family burden questionnaire. Both instruments have been adapted to the special needs of patients with type II diabetes and were

Dept. for General Practice and Health Services Research- University Hospital Heidelberg

„A multi-center, individual-level randomized, 18-month, parallel-group superiority trial to compare the efficacy of a complex primary care practice network-based care management intervention versus usual care in the improvement of self-care behavior among patients with type II diabetes and multiple comorbidities (GEDIMApplus)“

Version 1.0 – 29.10.2013

pretested before general application. CSSRI provides data on service utilization and refers to costs of health care provision and financial burden of informal care. Direct and indirect costs will be measured and analyzed from a societal perspective.

For an overview of all instruments used in this study to capture primary and secondary outcomes see Table 1. Physician reported secondary outcomes (HbA1c, events of hypoglycemia) are reported via a chart-review (for details see Chapter 10: Data collection).

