The equity-efficacy ratio (45) (and respective 95 % confidence intervals) will be calculated as the ratio of effects at T1 on health outcomes (change in SDSCA score; HbA1c%; HRQL) between the highest and the lowest socioeconomic group (related education/income/subjective social status) for both groups (PTC vs. TAU) compared to To. Additional consideration of social group sizes will be ensured by calculating the concentration index (PTC vs TAU) and plotting concentration curves at To and T1 respectively.

Subgroup analysis for nominal social groups will be performed by means of interaction terms for migration status (Turkish migrants, non-Turkish migrants, participants without migration background) to be included in the regression equations for respective health outcomes (change in SDSCA score; HbA1c%; HRQL) at T. If the tests of subgroup interaction effects are significant below the 0.05 level, further analysis will be performed to check whether their effects are independent (46).

Statistical analyses related to secondary outcomes 8 and 9 (see pages 4-5) focus on the incremental cost effectiveness ratio (ICER) (47, 48). The ICER relates cost differential to outcome differential between intervention and control groups. Bootstrap methods model statistical uncertainty and the net-benefit approach is applied (49, 50). Maximum willingness to pay thresholds and cost-acceptability curves (51, 52) will be determined. Sensitivity analyses will provide information on robustness of assumptions.

Because no adjustments for multiple endpoints are planned, findings (especially those related to secondary outcomes and subgroup analyses(46)) will be interpreted with caution in view of the number of statistical tests undertaken. Only the result of the primary efficacy analysis will be interpreted in a confirmatory manner. Confirmatory subgroup analyses are not planned. No interim analysis with regard to efficacy will be done.

In case of missing data, multiple imputation will be used to complete the data set for analysis. A complete-case analysis will be performed to assess the influence of missing data and the value of adopting multiple imputation methods.

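### The equity-efficacy ratio is defined in opposite orders with different socioeconomic indicators, is built from within-arm change, and is unstable when the denominator change is small

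*Protocol*

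**What the plan says.** Secondary objective 7 (protocol section 2.2) asks "if the care management intervention is equitable in the distribution of potential health gains", for self-care behaviour, HbA1c and health-related quality of life at 9 months (T1).

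The outcome for this objective is defined twice:

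- **Secondary outcomes, no. 7.** The equity-efficacy ratio is "calculated as the ratio between the change (compared to To at T1) in SDSCA-G 'score' of items 1-10", and likewise for HbA1c and the EQ-Index, "among the lowest vs. highest socioeconomic group (including education, occupation, income and subjective social status) in both arms of the trial (PTC vs. TAU").
- **Section 11.2.** The ratio is of effects at T1 "between the highest and the lowest socioeconomic group (related education/income/subjective social status"), taken in each arm against baseline, with 95% confidence intervals.

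Section 11.2 adds a second equity analysis: "calculating the concentration index (PTC vs TAU) and plotting concentration curves at To and T1 respectively". It handles migration status by interaction terms in the regression models for the same three outcomes. It applies the two-level regression model of the primary analysis to secondary endpoints 1 to 6, which leaves out endpoint 7. Only the primary analysis is confirmatory.

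The only planning values for the self-care score (SDSCA-G) are in section 11.4: "we estimated a mean change of 0.5 days (standard deviation 2.0"), with a between-group effect size of 0.25.

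**The concern.** Three features of the definition cause trouble.

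1. **Direction and indicators.** One place names the lowest SES group first and the other names the highest first. A value of 2.0 could mean that the poorest gained twice as much as the richest, or half as much. Occupation appears in one list only, so who counts as lowest or highest may differ too.
2. **Contrast.** The objective concerns the intervention, but the ratio is formed from change since baseline inside each arm. Such change includes time trend, regression to the mean and the effect of completing the questionnaires, which section 3.3.1 says may alter behaviour in both arms.
3. **Stability.** A ratio of two small-subgroup mean changes behaves badly when the denominator is not clearly different from zero, and its sign does not show whether both groups improved or both worsened.

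At stake is whether the reported equity result can be read in one way only and attributed to the intervention.

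**Working it through.** **The plan's own figure.** Section 11.4: difference 0.5, SD 2.0, two-sided 5%, 80% power. The normal approximation gives 2 × (1.96 + 0.84)² × (2.0/0.5)², about 252 per arm. The exact t-test gives 252.1, rounded up to 253, or 506 in total, which reproduces the plan. 506 × 1.15 gives 582 (291 per arm). With 15% drop-out, 291 × 0.85 ≈ 247 per arm are analysed.

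**Direction.** Take changes of 0.3 days (lowest group) and 0.6 days (highest group) as an illustration. Lowest over highest gives 0.3/0.6 = 0.5; highest over lowest gives 0.6/0.3 = 2.0.

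**Sign.** Two improving groups (0.2 and 0.1) give 2.0. Two worsening groups (−0.2 and −0.1) also give 2.0.

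**Contrast.** Suppose usual care (TAU) changes by 0.1 days in the lowest group and 0.25 in the highest, and the intervention (PTC) adds 0.5 days in both. The intervention effect is then the same in both groups. Lowest over highest is 0.1/0.25 = 0.4 in TAU and 0.6/0.75 = 0.8 in PTC. Neither ratio is 1 and the two differ, although the effect does not vary with SES.

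**Stability.** Assumptions not in the protocol: equal-sized SES groups (halves, tertiles or quintiles) and the same true change in the two outer groups. With n = 247 × fraction, the standard error of a group mean change is SE = 2.0/√n. A Fieller 95% interval is bounded only if |denominator|/SE exceeds 1.96. So for true change m, P(unbounded) = Φ(1.96 − m/SE) − Φ(−1.96 − m/SE). The ratio is negative with probability 2p(1 − p), where p = Φ(−m/SE).

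| SES split | n per group per arm | SE (days) | 0.5/SE | Unbounded, change 0.5 | Ratio negative, change 0.5 | Unbounded, change 0 |
|---|---|---|---|---|---|---|
| Halves | 123.5 | 0.180 | 2.78 | 21% | 0.5% | 95% |
| Tertiles | 82.3 | 0.220 | 2.27 | 38% | 2% | 95% |
| Quintiles | 49.4 | 0.285 | 1.76 | 58% | 8% | 95% |

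A simulation with 253 per arm agrees. At a change of 0.5 and a true ratio of 1, the central 95% range of the ratio is 0.26 to 3.44 (halves), 0.05 to 5.03 (tertiles) and −3.31 to 7.79 (quintiles). At zero change it is roughly −13 to 13 for any split, and half of the ratios are negative. At 1.0 day the interval is bounded in 99.6% (tertiles) or 94.5% (quintiles) of draws.

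**Why 0.5 and 0.** Section 11.4 uses 0.5 days as the mean change per patient and, through 0.5/2.0 = 0.25, as the between-group difference. If both hold, change under TAU is about zero. The protocol does not say so.

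**The alternative.** The difference between the PTC−TAU effects in the two outer SES groups has SE = 2.0 × √(4/n) = 4/√n and half-width 1.96 × 4/√n. With 253 per arm this is 0.70 days (halves, n = 126.5), 0.85 (tertiles) or 1.10 (quintiles, n = 50.6). With 247 it is 0.71 for halves and 1.12 for quintiles. A ratio of the PTC−TAU effects would not help: at an effect of 0.5 days in both groups its Fieller interval is bounded in only 51% (halves), 37% (tertiles) or 24% (quintiles) of draws.

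**The case against.** The textual conflict could be called a slip. Section 11.2's phrasing does not strictly fix numerator and denominator, and reciprocal ratios carry the same information. That is fair, but a formula without a stated numerator still needs one, and the missing indicator is a separate difference.

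A reader might infer that the ratio in controls is pure noise because control change is near zero. The protocol does not support that as a fact. No expected change under TAU is given, section 3.3.1 allows behaviour change in both arms, and nothing comparable is stated for HbA1c or the EQ-Index. Nor is the sign of the ratio mostly chance in an arm that changes by 0.5 days: it is negative in at most about 8% of trials across the splits shown.

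It can also be said that TAU's ratio serves as comparator for PTC's, and that the concentration index compares the arms. The first does not hold, since equal intervention effects can produce different ratios, as shown. The second stands in part: the index does set PTC against TAU. But it is introduced to account for group sizes, and it does not give the intervention effect by SES group.

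Finally, the outcome is not confirmatory, and the number of SES groups and the interval method may properly be left to the statistical analysis plan. Both points stand and limit the weight of this finding.

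**Conclusion.** The point holds as a moderate one about a secondary, non-confirmatory outcome. Two parts rest on the text alone: the order of the groups and the indicator list conflict between the Secondary outcomes list and section 11.2, and the ratio is formed from within-arm change, so it does not estimate the PTC−TAU effect by SES group.

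The instability is conditional. At a 0.5-day change and SD 2.0, with 247 analysed per arm, the interval is unbounded in about 21% to 58% of trials, depending on an assumed split from halves to quintiles. At zero change, which the sample-size assumptions suggest for TAU but do not state, it is unbounded in about 95%. These figures concern SDSCA-G only.

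It would go too far to conclude that objective 7 cannot be answered. The concentration index contributes, and the ratio would be usable if change were about 1.0 day, twice the planning value.

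**What to change.** - State one direction (numerator and denominator) and one list of SES indicators, identically in Secondary outcomes no. 7 and section 11.2.
- Add a treatment-by-SES interaction to the section 11.2 multilevel model for each of the three outcomes, as already planned for migration status. Report it with its 95% CI as the main equity estimate: the difference in the baseline-adjusted PTC−TAU effect between the lowest and highest SES group, or per SES unit.
- Keep the ratio and the concentration index as descriptive measures.

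The cost is analysis work and wording; no new data, patients or visits are needed. There are two downsides. The cited ratio is no longer the headline equity measure. The interaction is always defined but imprecise: its half-width of about 0.70 days (halves) to 1.10 days (quintiles) exceeds the 0.5-day target effect, so it should be read as exploratory.
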